## 13.2 Secondary outcomes

1. Brief Pain Inventory, including pain severity and interference subscales.
2. Global Rating of Change.
3. Satisfaction with Treatment.
4. Depression, Anxiety and Stress Scale-21.
5. Insomnia Severity Index.
6. Treatment Credibility Questionnaire.
7. Healthcare utilisation diary, including consultations, imaging, and medication use.

# 14. Assessment schedule

Outcome assessments will be conducted by trained assessors blinded to treatment allocation. Assessments will take place at baseline, week 4, week 12, and week 24. Primary and secondary outcomes will be collected at each assessment time point where applicable.

| Outcome | Baseline | Week 4 | Week 12 | Week 24 |
| --- | --- | --- | --- | --- |
| Pain intensity | Yes | Yes | Yes | Yes |
| Oswestry Disability Index | Yes | Yes | Yes | Yes |
| Secondary outcomes | Yes | Yes | Yes | Yes |

# 15. Data collection and management

Data will be collected using paper-based questionnaires and transferred to a password-protected electronic database.

Data quality-control procedures will include double data entry, random verification of records, automated range checks, and review of missing or inconsistent data.

Each participant will be assigned a unique study identification number. Identifiable information will be stored separately from study data on encrypted or password-protected storage with restricted access. Only authorised study personnel will have access to identifiable participant information.

# 16. Sample size calculation

The sample size was calculated based on detecting a clinically meaningful between-group difference of 2 points on the 0-10 numerical rating scale for pain intensity. The assumptions were: standard deviation of 3, power of 80%, and two-sided alpha of 0.05.

This required 86 participants per group. Allowing for 20% attrition, the final target sample size is 208 participants, with 104 participants per group.

The study is powered based on the primary outcome of pain intensity. Although repeated measurements will be collected over time, the planned linear mixed-effects modelling approach will account for within-subject correlation and is expected to increase statistical efficiency.

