## 2.2 Secondary objectives

1. To compare the effects of active CSWD and sham CSWD on psychosocial outcomes and sleep disturbance.
2. To evaluate treatment credibility and participant satisfaction.
3. To assess healthcare utilisation and participant global impression of change.
4. To determine whether CSWD provides clinically useful additional benefit as an adjunct to standard physiotherapy in a resource-constrained setting.

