# 3. Study design

This study is a multicentre, two-arm, parallel-group, randomised, single-blind, sham-controlled clinical trial.

Participants will be randomly allocated in a 1:1 ratio to one of two groups: active CSWD plus standard physiotherapy, or sham CSWD plus standard physiotherapy.

Participants and outcome assessors will be blinded to treatment allocation. Treating physiotherapists cannot be blinded because active CSWD produces perceptible warmth.

Outcome assessments will be conducted at baseline, week 4, week 12, and week 24. The total follow-up period will be 24 weeks.

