# 17. Statistical analysis

All analyses will follow the intention-to-treat principle.

Primary outcomes will be analysed using linear mixed-effects models. The models will include group, time, and group-by-time interaction as fixed effects, and participant as a random effect.

Continuous secondary outcomes will be analysed using similar mixed-effects models where appropriate. Categorical outcomes will be analysed using logistic regression or chi-square tests. Post-hoc comparisons will be adjusted using Bonferroni correction where appropriate.

Missing data will be handled using Multiple Imputation by Chained Equations under the assumption that data are missing at random. The imputation model will include baseline outcomes, treatment allocation, and relevant demographic variables. At least 20 imputations will be generated.

To assess potential attrition bias, baseline characteristics of participants who complete the study and those who do not will be compared.

A per-protocol sensitivity analysis will include participants who complete at least 80% of treatment sessions. All statistical analyses will be conducted using SPSS version 29.0 or later. Statistical significance will be set at p < 0.05.

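### The stated inputs (2 points, SD 3, 80% power, two-sided 5%) need 36 to 37 per group, not 86, so section 16 does not justify the target of 208

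*Protocol*

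**What the plan says.** Protocol section 16 bases the calculation on "detecting a clinically meaningful between-group difference of 2 points on the 0-10 numerical rating scale for pain intensity". It continues: "The assumptions were: standard deviation of 3, power of 80%, and two-sided alpha of 0.05". The result is given as "This required 86 participants per group". An allowance for 20% attrition is then added, giving 104 per group and 208 in total. Section 3 fixes the allocation: "Participants will be randomly allocated in a 1:1 ratio to one of two groups".

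The only other remark in section 16 that bears on n is that the mixed model is expected to make the analysis more efficient. Section 17 mentions a Bonferroni correction, but only for post-hoc comparisons.

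**The concern.** The protocol prints both the inputs and the result of a standard two-group calculation, and the result is about 2.3 to 2.4 times what the inputs give. At least one of the difference, the SD, the power and the sample size is therefore misreported, or a factor was applied and not disclosed.

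Section 16 is the protocol's only justification for recruiting 208 people. As written, an ethics committee or a reader cannot tell why more than twice the number implied by the stated inputs is needed, or what difference the trial can reliably detect. The protocol prints the figures itself, so this is not a detail left to a statistical analysis plan.

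**Working it through.** **Inputs.** Difference 2 points, SD 3, power 80% and two-sided alpha 0.05 (section 16); two groups, 1:1 (section 3); 20% attrition (section 16).

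**Step 1: the plan's own figure.**

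n per group = 2 × (z₀.₉₇₅ + z₀.₈₀)² × SD² / difference²
= 2 × (1.960 + 0.842)² × 9 / 4 = 35.3, so 36.

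The t distribution gives 36.3, so 37. The stated 86 is not reproduced: 86/37 = 2.3 and 86/36 = 2.4.

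**Step 2: what the stated inputs imply after attrition.**
- 36/0.8 = 45 per group, 90 in total.
- 37/0.8 = 46.25, so 47 per group, 94 in total.
- The protocol plans 208.

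**Step 3: can another factor explain 86?** Normal approximation, 2 points and SD 3 unless noted.

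| Variant | n per group |
| --- | --- |
| One-sided 5%, 80% power | 28 |
| Two-sided alpha 0.025, 80% power | 43 |
| Two-sided alpha 0.05/3 (three primary outcomes), 80% power | 48 |
| Two-sided alpha 0.05/9, 80% power | 59 |
| Two-sided 5%, 90% power | 48 |
| Two-sided 5%, 95% power | 59 |
| Two-sided 5%, 99% power | 83 |
| Change score, SD 3 at each time, zero correlation, 80% power | 71 |
| Rank-test efficiency 0.955 to 0.864, 80% power | 38 to 43 |

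None gives 86 per group at the stated alpha and power. Attrition cannot be the explanation, because it is applied after the 86 (86 × 1.2 = 103.2, so 104). A gain in efficiency from the mixed model would lower n.

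**Step 4: what follows if SD 3 and n are right.**

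Power = Φ(difference / (SD × √(2/n)) − 1.960)
- n = 86: SD × √(2/86) = 0.4575, and 2/0.4575 − 1.960 = 2.41, so power is 99.2%.
- n = 83 (104 × 0.8 = 83.2): SD × √(2/83) = 0.4657, and 2/0.4657 − 1.960 = 2.33, so power is 99.0%.

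Difference detectable with 80% power = 2.802 × SD × √(2/n)
- n = 86: 2.802 × 0.4575 = 1.28 points (1.29 by t).
- n = 83: 2.802 × 0.4657 = 1.30 points (1.31 by t).

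At 83 per group, power for 1.5 points is 89% (t distribution).

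**Step 5: what follows if 2 points, 80% power and 86 are right.**

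SD = 2 / (2.802 × √(2/86)) = 2 / 0.427 = 4.68 (4.65 by t), against the stated 3.

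**Step 6: attrition.** 86/(1 − 0.2) = 107.5, so 108 per group would be needed to keep 86 evaluable. With 104 recruited and 20% lost, about 83 remain. At SD 3 this hardly changes the power, but the restated section should use consistent numbers.

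**The case against.** The strongest reply is that nothing is lost. If SD 3 is right, the trial has more power for 2 points than it claims. The slip introduces no bias and leaves the outcomes, eligibility and analysis untouched. That stands, and it limits the harm to an untraceable justification and to recruitment well beyond what the stated inputs need.

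Three stronger readings are tempting, and the protocol supports none of them.

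- *The stated power and the stated difference are both wrong, and the trial is really sized for a smaller effect.* The figures are only jointly inconsistent. An SD of about 4.65 would reconcile 2 points, 80% power and 86, so power of about 99% and a detectable difference of 1.3 points hold only if SD 3 is correct. At SD 4, for instance, 83 per group gives 89% power for 2 points.
- *The origin of 86 can be recovered.* A 1.5-point difference at 90% power needs 85.03, so 86, with the t distribution, but 85 with the normal approximation. A total of 86 (43 per group at two-sided alpha 0.025), or 2 × 36 × 1.2 = 86.4, comes equally close. These rival reconstructions are conjecture.
- *A difference far below 2 points would count as success.* Section 17 says "Statistical significance will be set at p < 0.05", and section 2.2 includes the objective "To determine whether CSWD provides clinically useful additional benefit as an adjunct to standard physiotherapy in a resource-constrained setting". Nowhere does the protocol say that a p-value alone settles that objective. A significant result below the target difference is also possible in a correctly sized trial: at 80% power the smallest significant difference is about 1.960/2.802 = 70% of the target.

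**Conclusion.** The point holds as an internal inconsistency in section 16. The stated inputs need 36 to 37 per group, or 90 to 94 in total after 20% attrition, against a stated 86 per group and 208 in total. This rests only on the protocol's own figures and the standard comparison of two means, and no stated adjustment closes the gap.

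Which figure is misreported cannot be determined from the protocol. The consequences are therefore conditional: about 99% power for 2 points and about 1.3 points detectable with 80% power if SD 3 and n are right, or an SD of about 4.65 if the difference, the power and 86 are right. It should be corrected, because the trial's size rests on this calculation alone.

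**What to change.** Before enrolment, restate section 16 with the inputs actually used, so that difference, SD, power, attrition and n agree. The sponsor should first establish which difference, SD, power and any further factor produced 86, and report those.

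If the stated inputs stand and 208 is kept, replace the 80% with what 208 delivers. With SD 3, two-sided 5% and 83 evaluable per group (104 less 20%), that is about 99% power for 2 points, 89% for 1.5 points and 80% for about 1.3 points. One sentence should then say why more than the 90 to 94 participants implied by the stated inputs are recruited.

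The cost is a rewording of one section. No extra patients are needed, and section 5 states that none has been enrolled. The only downside is that the stated justification changes.

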# 5. Recruitment period and study timeline

Recruitment is planned to begin in June 2026 and is expected to be completed by June 2027. The final 24-week follow-up assessment is expected to be completed by December 2027. Data cleaning, analysis, and interpretation are expected to be completed by June 2028.

Based on patient flow at participating centres, each centre is expected to identify approximately 10-15 potentially eligible patients with CLBP per week. Recruitment of 208 participants across three centres is therefore considered feasible within the planned recruitment period.

No participants have been enrolled at the time of protocol submission.

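### The target of 104 per group does not absorb 20% attrition: a 20% loss leaves about 83 completers per group, three short of the 86 that the protocol says are required

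*Protocol*

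**What the plan says.** Section 16 of the protocol bases the sample size on "detecting a clinically meaningful between-group difference of 2 points on the 0-10 numerical rating scale for pain intensity", assuming "standard deviation of 3, power of 80%, and two-sided alpha of 0.05". It reports the result as "This required 86 participants per group" and then makes the attrition step: "Allowing for 20% attrition, the final target sample size is 208 participants, with 104 participants per group". No inflation formula is given. The section adds that the repeated-measures mixed model should improve efficiency, but puts no figure on the gain.

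Section 3 fixes equal allocation: "Participants will be randomly allocated in a 1:1 ratio to one of two groups". Section 5 carries the total forward into the feasibility statement: "Recruitment of 208 participants across three centres is therefore considered feasible within the planned recruitment period".

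Section 17 plans an intention-to-treat analysis with linear mixed-effects models and multiple imputation for missing data. Section 14 places outcome assessments at baseline and weeks 4, 12 and 24.

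**The concern.** An attrition rate is ordinarily a share of the people enrolled. Section 17 uses the idea in that sense when it plans to compare participants who complete the study with those who do not. Read this way, a target that allows for 20% attrition should still hold the required number once 20% of those enrolled have been lost. A target of 104 per group does not leave 86.

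At stake is the accuracy of a stated design property. A reader of Section 16 would take it that the trial can lose one participant in five over 24 weeks and still have the number it calls required. Its actual margin is narrower.

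**Working it through.** **Inputs, all from Section 16:** required number 86 per group; attrition 20%; target 104 per group, 208 in total; difference 2 points; SD 3; power 80%; two-sided alpha 0.05. Allocation is 1:1 (Section 3).

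**Step 1. Reproduce the stated target.**
- Multiplying: 86 × (1 + 0.20) = 103.2, rounded up to 104 per group, 208 in total. This matches the protocol exactly.
- Dividing: 86 / (1 − 0.20) = 107.5, rounded up to 108 per group, 216 in total. This does not match.

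**Step 2. Completers left at the stated target.**
- 104 × (1 − 0.20) = 83.2, about 83 per group.
- Shortfall: 86 − 83 = 3 per group, or 6 overall (166 against 172).

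**Step 3. Attrition that the target does absorb.**
- 1 − 86/104 = 18/104 = 17.3%.

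**Step 4. Effect on power, on the stated inputs.**
- The standardised difference is 2/3 = 0.667. A two-sample t-test at two-sided 0.05 has power 0.9915 with 86 per group and 0.9895 with 83. That is 99.2% against 99.0%.

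**Step 5. Check the 86 itself.**
- Normal approximation: n = 2 × (1.960 + 0.842)² × (3/2)² = 35.3, rounded up to 36 per group.
- t-test: 36.3, rounded up to 37 per group.
- The stated inputs therefore do not give 86. Neither do the variants tried: with the normal approximation and 80% power, one-sided testing gives 28, alpha 0.025 gives 43 and alpha 0.0167 gives 48; at two-sided 0.05, 90% power gives 48, 95% gives 59 and 99% gives 83.

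**Step 6. Effect on power if 86 is right for inputs not stated.**
- For 86 per group to give exactly 80% power at two-sided 0.05, the standardised difference must be about 0.43 (for example, 1.29 points at SD 3). At that effect, 83 per group gives about 78.6%, a loss of about 1.4 percentage points.

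**The case against.** Four objections deserve weight.

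- **The formula is not stated.** The phrase could loosely mean a 20% add-on to the required number, in which case 104 is consistent and only the wording is imprecise. It is right that the multiplication is inferred. The shortfall is not: it follows from 86, 20% and 104 alone once attrition is read as a share of those enrolled.
- **The count of 83 is of completers, not of participants analysed.** This stands. Under intention-to-treat with mixed models and multiple imputation, someone lost after week 4 or week 12 still contributes data. A reader might infer that only 83 per group would be analysed; Section 17 does not support that. Still, the protocol chose to add an attrition allowance to 86, and it gives no figure for the mixed-model gain that could stand in for the missing three.
- **The consequence is slight.** This also stands. A reader might infer that the trial is underpowered or must recruit 216. Neither follows. On the stated inputs power stays near 99%, and even on the least favourable reading the loss is about 1.4 points.
- **The 86 is the larger problem.** It is, and it should be settled first. It does not remove this point, because a corrected base number inflated by multiplication would repeat the same slip.

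The feasibility statement in Section 5 repeats 208 but contains no error of its own. At 10 to 15 potentially eligible patients per centre per week, 208 and 216 are about equally attainable.

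**Conclusion.** The attrition statement in Section 16 is wrong on the protocol's own figures. A 20% loss from 104 leaves about 83 completers per group, not 86, and 86 completers are retained only up to about 17% attrition. Nothing elsewhere in the protocol corrects it.

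The error is certain in its arithmetic and minor in its effect. It rests on two assumptions: that attrition means a share of those enrolled, and that 86 is taken as the protocol states it. The second is doubtful, since the stated difference, SD, power and alpha give about 36 to 37 per group. What the documents support is a misstated tolerance that should be corrected. They do not support a call for more participants or a claim of inadequate power.

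**What to change.** Keep 208 and change one sentence in Section 16. Either state that 104 per group retains 86 completers up to about 17% attrition, or state that 20% attrition would leave about 83 completers per group. Use the word completers, so that the sentence does not conflict with the analysis in Section 17.

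Before quoting any power at 83, reconcile the 86 with the stated inputs. Otherwise a power of about 99% would stand beside an 80% calculation made from the same difference, SD and alpha. If the base number changes, apply the allowance by dividing by (1 − attrition). For illustration, 36 / 0.80 = 45 and 37 / 0.80 = 46.25, rounded up to 47 per group.

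The rewording costs no participants and leaves the design unchanged. The stated tolerance becomes slightly less favourable. Section 5 says that nobody had been enrolled when the protocol was submitted, so the change could be made before recruitment.

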# 17. Statistical analysis

All analyses will follow the intention-to-treat principle.

Primary outcomes will be analysed using linear mixed-effects models. The models will include group, time, and group-by-time interaction as fixed effects, and participant as a random effect.

Continuous secondary outcomes will be analysed using similar mixed-effects models where appropriate. Categorical outcomes will be analysed using logistic regression or chi-square tests. Post-hoc comparisons will be adjusted using Bonferroni correction where appropriate.

Missing data will be handled using Multiple Imputation by Chained Equations under the assumption that data are missing at random. The imputation model will include baseline outcomes, treatment allocation, and relevant demographic variables. At least 20 imputations will be generated.

To assess potential attrition bias, baseline characteristics of participants who complete the study and those who do not will be compared.

A per-protocol sensitivity analysis will include participants who complete at least 80% of treatment sessions. All statistical analyses will be conducted using SPSS version 29.0 or later. Statistical significance will be set at p < 0.05.

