# 7. Eligibility criteria

## 7.1 Inclusion criteria

1. Age 18-65 years.
2. Male or female.
3. Diagnosis of chronic nonspecific low back pain persisting for at least three months.
4. Pain located between the 12th rib and inferior gluteal fold, with or without referred leg pain.
5. Average baseline pain intensity of at least 4 on a 0-10 numerical rating scale.
6. Ability and willingness to provide written informed consent.
7. Ability to attend treatment sessions and follow-up assessments.

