# 9. Randomisation and allocation concealment

Randomisation will be conducted using a computer-generated random allocation sequence. Permuted block randomisation with block sizes of 4 and 6 will be used and stratified by centre.

Allocation concealment will be maintained using sequentially numbered, opaque, sealed envelopes prepared by an independent researcher who is not involved in participant recruitment, treatment delivery, or outcome assessment.

After baseline assessment and informed consent, the treating physiotherapist will open the next sequential envelope to determine group allocation.

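### The primary mixed model omits centre, the stratification factor, and does not use the baseline score as a covariate

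*Protocol*

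**What the plan says.** Section 17 lists the terms of the primary model: "The models will include group, time, and group-by-time interaction as fixed effects, and participant as a random effect". It names no covariate, no residual covariance and no primary contrast, and does not say whether baseline is one of the levels of time. Otherwise section 17 uses baseline data only in the imputation model and in a comparison of completers with non-completers. Categorical outcomes go to logistic regression or chi-square tests, with no covariates named.

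Section 9 fixes the design: "Permuted block randomisation with block sizes of 4 and 6 will be used and stratified by centre". Section 4 names three centres. Section 3 gives the visits: "Outcome assessments will be conducted at baseline, week 4, week 12, and week 24". Section 7.1 requires "Average baseline pain intensity of at least 4 on a 0-10 numerical rating scale", while leg pain is optional at entry ("Pain located between the 12th rib and inferior gluteal fold, with or without referred leg pain").

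Section 16 sizes the trial for "detecting a clinically meaningful between-group difference of 2 points on the 0-10 numerical rating scale for pain intensity", taking an SD of 3, 80% power and a two-sided 5% level. It adds that "the planned linear mixed-effects modelling approach will account for within-subject correlation and is expected to increase statistical efficiency".

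**The concern.** Stratifying by centre removes between-centre variation from the comparison of arms, but the analysis gains from this only if centre is in the model. Without it, the standard error still carries variation that the design has removed. Likewise, each participant's baseline score is already collected and is normally the strongest predictor of the follow-up score. A model without it as a covariate compares either raw follow-up scores or changes from baseline, and neither is as precise as adjusting for it.

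There is also a conditional point. If baseline is a level of time and the participant effect is a random intercept with nothing added, the model assumes one variance at every visit. The entry rule restricts pain to 4–10 at baseline but not afterwards, so that assumption is doubtful for back pain.

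At stake are the width and, to a small degree, the calibration of the primary confidence intervals. Randomisation protects the estimates from bias under any of these models.

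**Working it through.** The protocol gives one SD (3) and no correlations or centre variances. All other SDs, correlations and ICCs below are assumptions, shown as ranges.

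**1. Baseline adjustment.** Let s_b and s_f be the baseline and follow-up SDs and r their correlation. Up to the common factor 2/n, the variances of a single-visit contrast are:
- raw follow-up: s_f²
- change: s_b² + s_f² − 2·r·s_b·s_f
- baseline-adjusted: s_f²·(1 − r²)

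Raw against adjusted is 1/(1 − r²): 1/0.91 = 1.10 at r = 0.3 and 1/0.64 = 1.56 at r = 0.6, so 10–56% more variance.

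Change against adjusted with equal SDs is 2/(1 + r): 1.54 at r = 0.3 and 1.25 at r = 0.6, so 25–54% more.

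Change against adjusted with s_b = s_f/2 is (1.25 − r)/(1 − r²): 0.95/0.91 = 1.04 at r = 0.3, 0.75/0.75 = 1.00 at r = 0.5 and 0.65/0.64 = 1.02 at r = 0.6, so 0–4% more.

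**2. Centre.** If centre accounts for a share ICC of the outcome variance, leaving it out inflates the standard error of a time-point contrast by 1/√(1 − ICC). This is 1.005 at ICC 0.01 and 1.054 at ICC 0.10, so 0.5–5% too large, with true two-sided error falling from 5% to about 4.9% and 3.9%. A centre effect that is the same at every visit cancels from within-participant change, so the change contrast is unaffected.

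**3. Equal variance.** Scores confined to 4–10 have an SD of at most 3, reached only if half score 4 and half score 10. A uniform spread gives 6/√12 = 1.73, or 2.0 on whole numbers. A baseline SD below 3 is therefore expected.

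Take 83 completers per arm (104 × 0.8), baseline SD 1.5 and follow-up SD 3. A random-intercept model pools the four visits to (2.25 + 3 × 9)/4 = 7.31. Its standard error for a time-point contrast is √(2 × 7.31/83) = 0.42, against a true √(2 × 9/83) = 0.47, with type I error about 7.7%.

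| Setting | Time-point contrast, type I error | Change contrast, type I error |
| --- | --- | --- |
| Closed form, baseline SD 1.5–2, follow-up SD 2.5–3 | 6.2–7.7% | 5.4–8.2% |
| Simulation, scores rounded to 0–10, baseline truncated at 4, 4,000 trials per setting | 5.8–6.8% | 3.7–5.0% |

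For the change contrast, the direction reverses between two reasonable sets of assumptions.

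**4. Efficiency in section 16.** With s_b = 1.5 and s_f = 3, change against raw is 1.25 − r, which is 0.95 to 0.65 over r = 0.3 to 0.6: 5–35% less variance. Averaging three follow-ups with mutual correlation 0.55–0.70 gives (1 + 2ρ)/3 = 0.70 to 0.80: 20–30% less. With s_b = 2 and r = 0.3, change against raw is (4 + 9 − 3.6)/9 = 1.04, slightly worse. The gain depends on the contrast and the SDs, but the listed terms can deliver it.

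**5. Power.** On section 16's inputs, 2 × (1.96 + 0.84)² × 3²/2² = 35.3, so 36 per group. The stated 86 does not reproduce, which is a separate matter. With 83 completers per arm, power for 2 points is about 99%.

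**The case against.** The strongest reply is that most of this is a matter of specification that a protocol may leave to the SAP. Section 17 does not say random intercept only, fixes no residual covariance, and does not say whether baseline is a time level. A reader might infer that the model forces equal variances and so yields wrong standard errors. The text does not support that: the equal-variance problem needs both baseline in the response and no richer covariance. It is also limited to the entry pain score, so it bears on back pain and not directly on leg pain or disability, which have no entry threshold. Section 16 does not tie its SD of 3 to any visit. The errors can also offset: with baseline SD 2, follow-up SD 3 and 10% centre variance, the time-point standard error is √(7.75/9) × 1.054 = 0.98 of the true one, and type I error is about 5.5%.

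The reply is also right that change from baseline is a form of adjustment. Truncation and loss of precision pull against each other: if truncation makes the baseline SD small, the change contrast loses almost nothing. The 25–54% loss needs equal SDs, which is more plausible for disability.

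What survives is that section 17 does list the model terms. That list leaves out the stratification factor and any baseline covariate, and an SAP that follows it inherits both gaps.

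**Conclusion.** The point holds as a shortfall in the stated primary model: centre and a baseline covariate should be in it. The avoidable variance is 10–56% for a raw follow-up contrast. For a change contrast it ranges from 0–4% (baseline SD half the follow-up SD) to 25–54% (equal SDs), at assumed correlations of 0.3–0.6. Omitting centre costs about 0.5–5% in time-point standard errors at an assumed ICC of 1–10%, on the conservative side, and nothing for change contrasts under a constant centre effect. The equal-variance concern is conditional, modest and without a fixed sign.

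Three stronger conclusions do not follow. The standard errors cannot be called wrong in a definite direction. Section 16's expected efficiency gain is not ruled out by this model. Power for the 2-point difference is not at risk on the protocol's own inputs.

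**What to change.** In section 17, specify the primary model as follows:
- response: the outcome at weeks 4, 12 and 24
- fixed effects: group, categorical time, group-by-time, baseline value of that outcome, baseline-by-time, and centre
- covariance: unstructured across the three visits within participant

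A constrained-baseline model (baseline kept in the response, arm means set equal there, unstructured covariance over four visits, centre included) is an equivalent choice. Include centre in the logistic models for categorical outcomes, and in the imputation model so that it matches the analysis.

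The cost is wording. Every variable is already collected, section 5 reports that no one was enrolled at submission, and the model can be fitted in the named software. It adds five fixed-effect parameters (two for centre, one for baseline, two for baseline-by-time) and uses six covariance parameters instead of two, which is small against 166 to 208 participants.

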# 2. Objectives

## 2.1 Primary objective

To determine whether continuous shortwave diathermy combined with standard physiotherapy is more effective than sham shortwave diathermy combined with standard physiotherapy in reducing pain intensity and disability in patients with chronic low back pain.

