# 13. Outcome measures

## 13.1 Primary outcomes

1. Back pain intensity measured using a 0-10 numerical rating scale.
2. Leg pain intensity measured using a 0-10 numerical rating scale.
3. Activity limitation measured using the Oswestry Disability Index.

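### Three primary outcomes at three follow-up visits, with no primary visit, contrast or success rule, leave the primary error rate above 5% on most readings (about 8–14%, up to 24–34%)

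*Protocol*

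**What the plan says.** - **Objective (Protocol section 2.1).** The comparison is of effectiveness "in reducing pain intensity and disability in patients with chronic low back pain". No visit is given, and nothing says whether both must improve or either suffices.
- **Primary outcomes (section 13.1).** Three are listed with equal standing: "Back pain intensity measured using a 0-10 numerical rating scale", "Leg pain intensity measured using a 0-10 numerical rating scale" and "Activity limitation measured using the Oswestry Disability Index".
- **Visits (section 14).** "Assessments will take place at baseline, week 4, week 12, and week 24". None of the three follow-up visits is singled out.
- **Sample size (section 16).** "The study is powered based on the primary outcome of pain intensity". This is one outcome, not identified as back or leg pain and not tied to a visit, planned at an undivided two-sided 0.05.
- **Analysis (section 17).** Each primary outcome gets a mixed model with group, time and their interaction. "Statistical significance will be set at p < 0.05". The only statement on multiplicity is "Post-hoc comparisons will be adjusted using Bonferroni correction where appropriate". It does not define the post-hoc comparisons and does not mention the three primary outcomes.

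**The concern.** Section 13.1 has three primary outcomes and section 16 has one, so the protocol disagrees with itself on what the trial is meant to show. Each fitted model offers a group effect, an interaction, and a between-group contrast at each of three visits. Across three outcomes that makes nine visit contrasts, and none is designated in advance.

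If any significant primary result may be reported as success, the chance of a false claim exceeds the nominal 5%. Outcome, visit and model term could also be chosen after the results are known. That matters in a trial justified by inconsistent earlier findings (section 1).

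**Working it through.** **1. The protocol's own figure.** Section 16 gives a difference of 2, SD 3, two-sided 0.05 and 80% power, and states 86 per group. The usual formula is n = 2 × SD² × (z₁₋α/₂ + z₁₋β)² / difference².

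- 2 × 9 × (1.960 + 0.842)² / 4 = 35.3, so 36 per group. The stated 86 is not reproduced.
- The same formula gives 48 per group at 0.05/3 and 59 at 0.05/9.

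The mismatch is a separate matter and does not change the multiplicity result. It does mean that the planned size exceeds what an adjusted alpha needs on these inputs.

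**2. Error rate if tests were independent.** P(at least one false positive) = 1 − (1 − 0.05)^k.

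- k = 3: 1 − 0.95³ = 14.3%
- k = 9: 1 − 0.95⁹ = 37.0%

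**3. Error rate with correlated tests.** The protocol gives no correlations, so these are assumptions. Nine normal test statistics were simulated with no treatment effect anywhere, using a product structure (outcome correlation × visit correlation). The moderate range takes visit correlation 0.4–0.7 and outcome correlation 0.2–0.6. The wide range takes 0–0.8 and 0–0.7. Any one significant result counts as a positive.

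| Reading of section 17 | Moderate range | Wide range |
| --- | --- | --- |
| One test per outcome, outcomes unadjusted | 12–14% | 10.9–14.3% |
| Bonferroni over the three visits within each outcome, outcomes unadjusted | 10–13% | 8.0–14.0% |
| All nine visit contrasts unadjusted | 24–34% | 20.4–37.0% |
| As the row above, counting only results favouring active CSWD | 12–18% | 10.2–20.4% |
| Bonferroni over all nine contrasts | 3.6–4.7% | 3.0–4.9% |

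All rows except the fourth count false positives in either direction.

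**4. Power left after control.** Evaluable per group after 20% attrition: 104 × 0.8 = 83.2, taken as 83. Noncentrality = 2 / (3 × √(2/83)) = 4.29, with 164 degrees of freedom.

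- Two-sided 0.05: power 99.0%
- Two-sided 0.05/3: power 96.9%

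**5. Power if every result had to be significant.** Assume the same standardised effect (2/3) for every test. The chance that one test fails is 1 − 0.9895 = 0.0105 (0.01046 before rounding). The Bonferroni lower bounds on joint power are:

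- three outcomes at one visit: 1 − 3 × 0.01046 = 96.9%
- nine contrasts: 1 − 9 × 0.01046 = 90.6%

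Simulation over the moderate range gives about 97% and 92–95%. Both exceed the stated 80%.

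**The case against.** **Section 17 may already adjust the visit contrasts.** After a group-by-time model, between-group comparisons at each visit are commonly what is meant by post-hoc comparisons. This stands. A reader might infer that the protocol commits to nine raw tests and hence to a false positive rate of one in four to one in three, but the text does not establish that. It is the least favourable reading. Even so, adjusting over visits leaves the three outcomes unadjusted, at about 8–14%.

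**The objective's wording could mean that pain and disability must both succeed.** If every primary outcome had to be significant, the error rate would be at most 5%. The protocol states no such rule, and it has two pain outcomes without saying which is meant.

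**Such detail can be left to a statistical analysis plan.** This is fair for the details of alpha allocation, and no analysis plan was available here. It does not cover the conflict between sections 13.1 and 16, or the missing primary visit on which the sample size should rest.

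**Two stronger criticisms are tempting but unsupported.**

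- A reader might infer that requiring all outcomes to succeed would push power well below 80%. On the protocol's inputs it does not (step 5). It could do so only if effects on leg pain, disability or later visits were smaller, and the protocol gives no planning values for these.
- A reader might infer that the interaction test would miss a constant benefit. That requires baseline to be left out of the time factor. Section 17 does not say so, and section 14 lists baseline among the assessments.

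**Conclusion.** The point holds. The protocol contradicts itself on what is primary and names no primary visit, contrast or success rule. The two-sided familywise error is about 8–14% on the milder readings and about 24–34% (37% if independent) if no visit contrast is adjusted. False positives favouring active CSWD are about half the nine-test figure. Only an all-must-succeed rule or Bonferroni over all nine contrasts keeps the rate at or below 5%, and the protocol states neither.

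The ranges rest on assumed correlations and on any single significant result counting as success. The existence of the defect does not depend on the correlations. The power figures rest on 2 points, SD 3 and 83 evaluable per group. They speak to numerical-rating-scale pain only, since section 16 gives no inputs for disability.

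**What to change.** Before the first enrolment:

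1. Make sections 2.1, 13.1 and 16 agree on what is primary, and say in section 16 whether the powered outcome is back or leg pain, and at which visit.
2. Name one primary time point.
3. In section 17, name the between-group contrast at that visit, estimated from the mixed model, as the primary test.
4. Then choose one of two routes:
   - one primary outcome at two-sided 0.05, with the others tested in a fixed sequence or made secondary; or
   - all three outcomes kept primary, with Holm across them at the named visit.
5. Say which comparisons the Bonferroni sentence covers, and drop the qualifier that leaves its use open.

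Which outcome and visit become primary is for the sponsor to decide.

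**Cost.** Section 5 reports no enrolment so far, so this is a wording change in the protocol, and in the registry entry where it carries the same text. On the stated inputs no extra participants are needed: Holm's strictest step, 0.05/3, leaves 96.9% power. The downside is that outcomes and visits moved to secondary can no longer carry the primary claim.
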